### Analyses of secondary outcomes

The secondary endpoints comprise time-to-event measures, discrete measures and continuous measures. Short descriptions of the methods to be used for each secondary outcome are detailed in Table 1.

As noted earlier, conventional statistical methods for the analysis of survival data assume that competing risks are absent. Given that the clinical outcomes (and adverse and serious adverse events) represent competing risks, the results from a sub-distributional hazard model will also be reported as has been recommended for RCTs [40, 41].

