Time from randomisation to hospitalisation for which the primary coded reason for admission is presumed or confirmed acute gastroenteritis or acute diarrhoea illness before age 36 months;Time from randomisation to hospitalisation for which the primary reason for admission is rotavirus-confirmed diarrhoea illness before age 36 months; andTime from randomisation to rotavirus infection (not necessarily requiring hospitalisation) that meets the jurisdictional case definition (for disease notification) before age 36 months.

Immunological outcomes comprise:
Change in anti-rotavirus IgA log titre between administration of the Rotarix or placebo dose and 28 to 55 days post dose.

Safety outcomes comprise:
The occurrence of intussusception fulfilling Brighton criteria [24] within the first 28 days after administration of the Rotarix or placebo dose; andSerious adverse events as defined by [25] between randomisation and age 36 months.

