### Competing risks

Conventional statistical methods for survival analysis assume independent or noninformative censoring. However, the presence of competing risks violates the noninformative censoring assumption because the occurrence of one event influences the likelihood of a competing event from occurring [26]. While the co-primary time-to-event outcome defined here does not compete with any other event, the secondary clinical time-to-event outcomes and safety outcomes may represent competing risks. This is true even though the secondary clinical outcomes are not strictly mutually exclusive as it is sufficient that the occurrence of one event influences the probability of subsequent events of a different type for the competing risks context to be relevant.

Competing risks require special handling, and we return to this topic in a later section.

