### Safety and adverse events

Two safety and tolerability outcomes are defined in the protocol: the occurrence of intussusception within the first 28 days after randomisation and the occurrence of serious adverse events between randomisation and 36 months. The occurrence of intussusception will be reported in terms of frequency and proportion, by treatment arm and overall. The serious adverse events as defined by [25] will be reported as frequency and proportion, stratified by treatment arm and overall. While no analysis will be performed on the safety and adverse event data, they will be included in the competing risk sensitivity analysis mentioned earlier.

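### The supplementary competing-risk analysis counts overlapping secondary outcomes and all adverse events as competing events, although no non-fatal event prevents a later target event

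*SAP article*

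**What the plan says.** The section Competing risks sets the test. For the competing-risk setting to apply, "it is sufficient that the occurrence of one event influences the probability of subsequent events of a different type". It applies this to the secondary clinical outcomes and the safety outcomes while conceding their overlap: "This is true even though the secondary clinical outcomes are not strictly mutually exclusive". Of the clinical co-primary it says that "the co-primary time-to-event outcome defined here does not compete with any other event".

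Analyses of secondary outcomes then makes the commitment: "Given that the clinical outcomes (and adverse and serious adverse events) represent competing risks, the results from a sub-distributional hazard model will also be reported". Table 1 promises a competing-risk analysis for each of the three secondary time-to-event outcomes, after a main analysis in the form used for the clinical co-primary. Under Safety and adverse events, the safety data get no analysis of their own, but "they will be included in the competing risk sensitivity analysis mentioned earlier".

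The three outcomes, listed under Secondary, are hospitalisation for acute gastroenteritis or diarrhoea, hospitalisation for rotavirus-confirmed diarrhoea, and rotavirus infection meeting the jurisdictional case definition whether or not the child is admitted. SAEs are counted from randomisation to 36 months of age, with no restriction to fatal ones. Death is not named in any of these sections.

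**The concern.** A sub-distribution hazard model is built for events that end the possibility of the target event. A child who has the competing event first stays in the risk set to the end, as someone who can no longer have the target event. That is right for death. It is wrong for a non-rotavirus gastroenteritis admission, or an SAE from which the child recovers, because the child remains at risk and surveillance continues to 36 months of age. Dependence between two outcomes does not make them competing risks.

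The overlap adds a second difficulty. A rotavirus-confirmed diarrhoea admission would ordinarily also be a gastroenteritis or diarrhoea admission. One admission can then be target and competitor at the same moment, and the SAP gives no rule for its type.

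At stake is a published sensitivity result that omits recorded rotavirus or gastroenteritis events, and that may disagree with the main secondary analysis because of how events were classified.

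**Working it through.** The SAP gives no figure for this analysis, so there is none to reproduce. The calculation below illustrates size only.

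**Inputs from the SAP**
- Median time to gastroenteritis hospitalisation: 15 to 40 months from birth (Trial population). It is applied here from randomisation, a simplification.
- Follow-up T: age at vaccination is modelled as uniform from 6 to 12 months (Evaluation of operating characteristics), mean 9, so T = 36 − 9 = 27 months.

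**Assumptions not in the SAP**
- Rotavirus-confirmed share p of gastroenteritis admissions: 5% or 20%.
- Other SAEs, rate s: 0, 0.1 or 0.4 per child-year.
- Constant, independent hazards and first-event coding.

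**Formulas** (target: first rotavirus-confirmed admission)
- λ = ln 2 / median; target hazard r = pλ; competing hazard o = (1 − p)λ + s/12, per month.
- True incidence = 1 − exp(−rT).
- Counted incidence = r/(r + o) × [1 − exp(−(r + o)T)].
- Share lost = 1 − counted/true.

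**Worked case** (median 15, p = 20%, s = 0.1)
- λ = 0.6931/15 = 0.04621; r = 0.00924; o = 0.03697 + 0.00833 = 0.04530.
- True = 1 − exp(−0.2495) = 22.1%.
- Counted = (0.00924/0.05454) × [1 − exp(−1.473)] = 0.1694 × 0.771 = 13.1%.
- Lost = 1 − 0.1306/0.2208 = 41%.

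**All settings**

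| Median (months) | Rotavirus share | True incidence | Counted at s = 0 / 0.1 / 0.4 | Lost |
|---|---|---|---|---|
| 15 | 5% | 6.0% | 3.6 / 3.3 / 2.6% | 41 / 46 / 58% |
| 15 | 20% | 22.1% | 14.3 / 13.1 / 10.3% | 35 / 41 / 54% |
| 40 | 5% | 2.3% | 1.9 / 1.7 / 1.3% | 19 / 27 / 45% |
| 40 | 20% | 8.9% | 7.5 / 6.8 / 5.1% | 16 / 24 / 43% |

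**Effect on the ratio.** The sub-distribution hazard ratio is approximated by ln(1 − counted, vaccine) / ln(1 − counted, control).
- Vaccine acts on rotavirus admissions only (hazard ratio 0.5): the approximate ratio is 0.50 to 0.51, so almost no shift.
- Vaccine lowers rotavirus admissions by 40% (true ratio 0.60) and other gastroenteritis admissions by 20%, other SAEs unchanged. In the worked case the vaccine arm has r = 0.6 × 0.00924 = 0.00554 and o = 0.8 × 0.03697 + 0.00833 = 0.03791, so counted = (0.00554/0.04345) × [1 − exp(−1.173)] = 8.8%. The ratio is ln(1 − 0.0881)/ln(1 − 0.1306) = 0.0923/0.1400 = 0.66. Over the twelve settings the same formula gives 0.62 to 0.66.

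**Death and the co-primary.** The same incidence formulas are used, with r the hazard of medical attendance and o = −ln(1 − d)/27 for an assumed mortality d. At d = 1%, incidence moves from 60.8% to 60.5% (simulated median 20 months) and from 31.2% to 31.1% (median 50 months).

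**The case against.** Most of the case on the other side limits the reach of the point, and much of it stands.

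- **The main secondary analyses are sound on this point.** Table 1 gives each outcome its own time-to-event analysis in the co-primary's Weibull form. The censoring rules under Interim analyses of co-primary outcomes do not end follow-up at another admission or an SAE. A reader might infer that the trial's secondary results as a whole lose events. They do not: the sub-distribution model is reported in addition and is called a sensitivity analysis, of outcomes the SAP terms exploratory.
- **The coding is not stated.** Loss of events follows from standard first-event coding; the SAP does not say how it will code events. Nor is loss shown outcome by outcome. A rotavirus admission that is also a gastroenteritis admission cannot precede and remove a child's first gastroenteritis admission unless it is classed as a different type.
- **Some inputs are outside the document.** The SAE definition and the jurisdictional case definition are cited, not given, so how often one admission meets several definitions is unknown.
- **The simulated medians of 20 to 50 months are not the right rates.** A reader might use them for the competing event, but they describe medical attendance, the co-primary. The hospitalisation medians are the closer input.
- **The ratio need not be biased.** A reader might conclude that all three secondary hazard ratios would be wrong. That is not shown: the ratio barely moves if the vaccine acts on rotavirus alone.
- **Death is denied only by implication.** It may already fall within the SAEs in the secondary analysis, and censoring at the last known time in the study could accommodate it for the co-primary. A material bias in the co-primary cannot be inferred.

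None of this makes a non-fatal event a competing risk. Acknowledging that the outcomes overlap does not supply the missing condition.

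**Conclusion.** The concern holds as an error of definition that carries into a planned analysis. The test under Competing risks is wrong, and the sub-distribution analysis specified from it includes events that preclude nothing.

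If it is run as written with first-event coding, roughly 16 to 58% of children with a rotavirus-confirmed admission would have that event uncounted. The range rests on constant independent hazards and on the assumed rotavirus shares and SAE rates, so it shows the order of the problem and does not forecast it. The main harm is to incidence and event counts, and so to precision. The ratio is distorted as well if the vaccine changes the competing events. That case is relevant because the trial looks for benefit on all-cause gastroenteritis.

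The consequence is confined to an added sensitivity analysis of exploratory outcomes. The 0.97 decision rule, the interim triggers and the simulated type I error do not depend on it. For the co-primary, the point about death is conceptual: at most about 0.3 percentage points of incidence at an assumed 1% mortality. The change is worth making before the final analysis, but nothing in the trial's main conclusions turns on it.

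**What to change.** In Competing risks, Analyses of secondary outcomes, Safety and adverse events, and Table 1:

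1. Define a competing event as one that precludes the outcome, in practice death.
2. Remove the other clinical outcomes and non-fatal adverse and serious adverse events from the competing set. Fatal events remain.
3. In the sub-distribution model, as in the main analysis, count each outcome's own first event regardless of any earlier non-fatal event. State the event coding. One admission may then count for every outcome whose definition it meets.
4. Replace the statement that the co-primary competes with no other event by one noting that death precludes it, saying how a death is handled and that the expected numerical effect is very small.

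The cost is a change of wording and simpler analysis code. No new data are needed, and the simulations need not be rerun because they cover only the two co-primary endpoints.

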### Interim analyses of co-primary outcomes

Bayesian adaptive trials rely on accumulating data and pre-specified decision rules to trigger adaptations. However, in order to ensure trial integrity, extensive simulation of the trial is required to investigate and quantify the operating characteristics such as the type I error rates, power and expected sample size under a range of hypothetical trial scenarios.

In this section, we outline the decision processes used for the interim analyses. Details on the simulations that were used to evaluate the operating characteristics of the trial are provided in a later section.

A simplified flow chart for the interim analyses and decision rules is presented in Fig. 1. The first interim analysis on the immunological endpoint will occur when 70 participants have full (baseline and follow-up) immunologic results. Further interim analyses occur after every subsequent 50 children or after every 3 months, whichever occurs sooner, unless there have been no new entrants. If there are no new blood samples and/or events, then we will defer the full analysis until the next scheduled interim. Analysis of the clinical endpoint will start when 200 children are enrolled in order that there are enough events to meaningfully undertake a time-to-event analysis.

**Fig. 1 Fig1:**
[figure not shown]
Process flow diagram for interim analyses and decision rules

After the maximum number of participants with immunological samples (*n* = 250) has been collected and processed, we will continue to conduct interim analyses every 3 months using the accumulating clinical outcome data until a statistical trigger occurs or the maximum sample size is reached.

The data for assessing the clinical outcomes and/or serious adverse events is obtained from surveillance, which is ongoing until 36 months of age. In brief, each participant’s medical records are checked within 28 to 55 days of vaccination and then every 6 months after vaccination. When medical care cannot be identified, we will make direct contact with the participant’s legally responsible caregiver and/or treating physician to determine whether medical attendance or serious adverse events occurred.

Censoring is complicated by virtue of the intermittent surveillance on each participant; this is especially the case for the interim analyses. At each interim analysis, for participants (1) not yet having had an event, (2) less than 36 months of age and (3) not considered lost to follow-up, we will censor at the time of the last surveillance time. Participants will be censored at 36 months of age if they have not had an event, and if lost to follow-up, censored at the last known time to be in the study. If no surveillance has occurred for an enrolled participant at the time of an interim analysis, then we will not use their data for estimating the posterior.

At each interim analysis up to *n* = 250, we will have incomplete immunological results on the enrolled participants. Additionally, many participants will not have reached the clinical endpoint nor completed follow-up. In order to incorporate all of the available information into the decision framework, we make use of posterior predictive distributions to generate simulated data conditional on our posterior parameter estimates. This process enables us to impute values for subjects with incomplete results [13].

For the immunological outcome, we will compute the joint posterior distribution of the model parameters using methods detailed earlier, namely a logistic regression model with an indicator variable for treatment status. We will use all the available data with complete immunological results.

Next, we will test for futility by computing the predictive probability of observing a treatment effect under the assumption that we continue to the maximum sample size (*n* = 250) for the immunological endpoint. A predictive probability is computed using the following steps.
Take a draw from the joint posterior distribution.Use the draw to simulate random variables from a Bernoulli distribution to impute the immunological results that are not yet available for the enrolled participants with pending immunological results and the immunological results for future participants that are currently unenrolled up to the maximum sample size of 250.Combine the observed and the simulated data to form a complete dataset.Fit a logistic regression model to the complete dataset and compute the probability that the treatment effect is above zero.If the probability that the treatment effect is greater than zero is above a threshold value, then consider the trial successful and increment a counter of the number of successful trials.Go back to step 1, repeating the process at least 1000 times.

At the end of the process, we know the number of times that the trial was deemed successful from which we can compute the probability of predicted success (PPoS) as:
6$$\begin{array}{*{20}l} \textrm{PPoS}= \frac{1}{k} \sum_{1}^{k} \mathrm{I}[\mathbb{P}(\beta_{\text{trt}}>0)>0.97] \end{array} $$

where I() represents an indicator function evaluating to 1 if the contained expression is true and 0 otherwise, *β*_trt_ is the log odds ratio of seroconversion in the treatment arm versus the control arm and *k* is the total number of simulated datasets. If the PPoS is less than the futility threshold, then stop for futility and cease enrolment.

Next, if futility was not established, repeat the above process; however, only impute for the enrolled participants that do not yet have complete immunological data. If the resultant PPoS is greater than the threshold to stop venous sampling, we will cease venous sampling. If either the futility or stop venous sampling thresholds are triggered, we will undertake a final analysis on the immunological outcome once all the enrolled participants (at the time of the trigger) have been followed to completion.

Assuming that the trial has not been stopped for futility, we will start analysing the clinical endpoint at the next scheduled interim analysis after 200 participants have enrolled. The interim analysis process for the clinical outcome is similar to that of the immunological outcome, but with the added complication of censoring.

First, we will compute the joint posterior distribution of the model parameters using methods detailed earlier, namely a Weibull proportional hazards model with an indicator variable for treatment status. To compute the posterior, we will use the data from all participants that have had at least one surveillance visit.

Next, we will test for futility by computing the predictive probability of observing a treatment effect under the assumption that we continue to the maximum sample size (*n* = 1000) for the clinical endpoint. A predictive probability is computed using the following steps.
Take a draw from the joint posterior distribution.Use the draw to simulate random variables from a left-truncated Weibull distribution to impute the event times for the enrolled participants that are not yet censored due to age but are yet to have an event. Additionally, use the draw to simulate the event times from a Weibull distribution for the participants not yet enrolled, up to the maximum size (*n* = 1000).If the simulated event times occur after the participant is 36 months old, then censor at 36 months less the age of enrolment, which, if unknown, is drawn from a uniform distribution between 6 and 12 months.Combine the observed and the simulated data to form a complete dataset.Fit a Weibull proportional hazards model to the complete dataset and compute the probability that the treatment effect is below zero.If the probability that the treatment effect is below zero is above a threshold value, then consider the trial successful and increment a counter of the number of successful trials.Go back to step 1, repeating the process at least 1000 times.

At the end of the process, we know the number of times that the trial was deemed successful from which we can compute the probability of predicted success (PPoS) as:
7$$\begin{array}{*{20}l} \textrm{PPoS}= \frac{1}{k} \sum_{1}^{k} \mathrm{I}[\mathbb{P}(\theta_{\text{trt}}<0)>0.97] \end{array} $$

where I() represents an indicator function evaluating to 1 if the contained expression is true and 0 otherwise, *θ*_trt_ is log hazard ratio for the treatment effect and *k* is the total number of simulated datasets. If the PPoS is less than the futility threshold, then stop for futility and cease enrolment.

Next, if futility was not established, repeat the above process; however, only impute for the enrolled participants that have not yet had an event or have not yet had a visit and are not censored for age. If the imputed event times fall beyond the time of the interim or age to 36 months, then censor appropriately. If the resultant PPoS is greater than the expected success threshold, we will cease the trial for expected success. If either futility or expected success thresholds are triggered, we will undertake a final analysis on the clinical outcome once all the enrolled participants (at the time of the trigger) have been followed to completion.

If none of the above rules are met, we continue enrolling (up to 1000 participants) and venous sampling (up to 250 participants).

If we observe a treatment effect associated with the immunological but none for the clinical outcome, we will conclude that a positive immunological effect has been conferred, but a clinically meaningful benefit has not been demonstrated. If we observe neither immunological nor clinical treatment effects, we will deem the trial to have not met our predefined decision thresholds, but report on the observed probabilities of immunological and clinical treatment effects.

As documented in the protocol [42], the trial may also be stopped at any point at the discretion of the coordinating principal investigator (CPI) or the trial sponsor. The DSMB will advise the CPI according to pre-determined stopping rules or unanticipated safety concerns.

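### At later interims, event-free children past 36 months are censored at 36 months on age alone, so months not yet reviewed count as event-free; the effect is small unless no record check covers the time to 36 months

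*SAP article*

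**What the plan says.** The rules stand in the SAP article, section on interim analyses of co-primary outcomes, in the text after Fig. 1.

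- Surveillance schedule: "medical records are checked within 28 to 55 days of vaccination and then every 6 months after vaccination". Data come from "surveillance, which is ongoing until 36 months of age".
- Event-free, under 36 months of age and not lost to follow-up: "we will censor at the time of the last surveillance time".
- Event-free at 36 months or older: "Participants will be censored at 36 months of age if they have not had an event".
- The one exception: "if lost to follow-up, censored at the last known time to be in the study".

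The futility step for the clinical endpoint then uses posterior draws to "impute the event times for the enrolled participants that are not yet censored due to age but are yet to have an event". The expected-success step likewise leaves out children already censored for age. If a stopping threshold is met, the final clinical analysis is done "once all the enrolled participants (at the time of the trigger) have been followed to completion".

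**The concern.** The schedule is anchored to the dose and the endpoint window to age, so a check seldom falls on the 36-month birthday. A child dosed at 9 months is due for checks at about 15, 21, 27, 33 and 39 months of age. Suppose that child is event-free at the 33-month check. At an interim when the child is 35 months old, the plan censors at 33 months and imputes forward. At an interim when the child is 37 months old, with nothing new reviewed, the plan censors at 36 months and imputes nothing. Three months that nobody has looked at become event-free follow-up.

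The paragraph recognises that intermittent surveillance complicates censoring and handles younger children correctly. It does not extend the same care to older ones. What could be affected is the estimated hazard (too low), the medians (too long), the Weibull shape (pulled below its true value by an artificial event-free tail) and the predictive probabilities, which treat these children as fully observed. The secondary time-to-event outcomes follow the same form of analysis (Table 1).

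**Working it through.** The plan gives no figure for this point, so there is none to reproduce. The inputs are the 6-monthly checks from vaccination (interim analyses section) and, from the section on operating characteristics, age at vaccination *a* uniform on 6 to 12 months, exponential event times, control medians of 20 to 50 months, and accrual of about 30 or 50 per quarter. Randomisation and vaccination are treated as simultaneous.

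**The gap.** The last check before 36 months comes 24 months after the dose, at age *a* + 24. The gap is 36 − (*a* + 24) = 12 − *a*, which runs from 0 to 6 months with mean 3. Mean follow-up is 36 − 9 = 27 months, so the gap is 3/27 = 11% of it. The gap exceeds 3 months in half the children.

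**When it starts.** Clinical interims begin at 200 enrolled: 200/50 = 4 quarters (12 months) or 200/30 = 6.7 quarters (20 months). The oldest child is then at most 12 + 12 = 24 or 12 + 20 = 32 months old. Only later interims are affected.

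**Case B: the next 6-monthly check takes place (assumption).** That check falls at age *a* + 30, so a child waits *a* − 6 months past the 36-month birthday, on average 3. The number affected at one interim is about monthly accrual × 3 × the proportion event-free at 24 months, with S(t) = 2^(−t/m).

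- 30 per quarter, medians 20 vs 30: 10 × 3 × (0.435 + 0.574)/2 = 15.
- 50 per quarter, medians 35 vs 50: 16.7 × 3 × (0.622 + 0.717)/2 = 34.

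Simulation (400 trials per setting, exponential model, normal approximation to the posterior) gives the same 15 to 34 children during accrual, about 0.4 to 1.3% of person-time. Compared with censoring at the last check, medians differ by about 0.5 month or less and hazard ratios by 0.002 or less.

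**Case A: no check covers the time from the last visit to 36 months (assumption).** The share of events missed is mean[S(24) − S(36 − a)] / mean[1 − S(36 − a)]. For m = 35: S(24) = 0.622 and mean S(36 − a) = 0.586, so 0.0355/0.4138 = 8.6%. With the gap counted as event-free, the constant-hazard rate is (1 − S(24)) / [(1 − S(24))/λ + 3·S(24)], with λ = ln 2/m. For m = 35 this is 0.3783/(19.10 + 1.87) = 0.01804 per month, an apparent median of 38.4. The last two columns fit the plan's Weibull form by maximum likelihood to 400,000 exponential event times (true shape 1).

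| True median (months) | Events missed | Apparent median, constant hazard | Weibull shape | Weibull median |
|---|---|---|---|---|
| 20 | 7.0% | 21.6 | 0.93 | 21.7 |
| 35 | 8.6% | 38.4 | 0.91 | 40.3 |
| 50 | 9.3% | 55.3 | 0.91 | 60.1 |

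Censoring the same data at the last check returns a shape of 1.00 and medians of 20.0, 35.0 and 50.1.

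**Treatment comparison in Case A.** By the same rate formula, the hazard ratio for 35 vs 50 months reads 0.695 (true 0.700), for 35 vs 45 months 0.774 (true 0.778) and for 20 vs 30 months 0.659 (true 0.667). The simulations showed no type I error inflation beyond Monte Carlo noise.

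**A shorter median.** The Background reports that 77% of children in remote communities attend a clinic for diarrhoea before their first birthday. A constant hazard matching this has median 12 × ln 2 / −ln(0.23) = 5.7 months. The missed share is then 1.6%, even with no closing check.

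**The case against.** The strongest reply is that the sizeable figures need an assumption the document does not make. The schedule is stated as every 6 months after vaccination, with no stop at 36 months. Surveillance that is ongoing until that age describes the window being observed, not the last date on which records may be read: a retrospective review at 39 months captures events up to 36. The final analysis waits until children are followed to completion, and the data monitoring section places it after study completion and database lock. If records have by then been reviewed to 36 months, censoring there is ordinary administrative censoring and correct. The article gives the schedule only in brief, so a missing closing check in this text is not evidence that none is planned.

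This stands. A reader might infer from the rule that the final analysis will lose 7 to 9% of events; the document does not support that. A reader might also infer a biased treatment comparison. The rule is blind to arm, every clinical decision rests on the posterior probability that the log hazard ratio is below zero, and the hazard ratio moves by less than 0.01 even in the worst case.

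The outcome counts any clinic presentation, so its median may be much shorter than 20 to 50 months. That also stands, with the caution that the 77% figure is for the first year of life in remote communities, and a hazard that falls with age would raise the 1.6%.

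The plan also accepts that interim data may later be amended, for less than 5% of the sample. That tolerates data corrections. It does not justify a rule that counts unreviewed time as reviewed.

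None of this removes the interim defect: the 36-month rule depends on age alone, and the imputation step passes these children over.

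**Conclusion.** The rule as written is wrong for intermittently observed children at interims once some have passed 36 months, and it is inconsistent with the rule for younger children in the same paragraph. Severity is minor. If 6-monthly checks continue past 36 months, the effect is confined to interims and small (Case B). The larger loss of events, longer medians and Weibull shape of about 0.91 to 0.93 (Case A) apply to the final analysis only if no check covers the time to 36 months, which the document does not say. The hazard ratio is nearly unaffected in both cases, so at stake are interim predictive inputs and, conditionally, the reported medians and hazard shape.

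These sizes assume uniform dosing age, checks exactly on schedule, exponential event times and the plan's simulated medians. The simulations approximate the planned Weibull MCMC analysis, so their figures are indicative.

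**What to change.** Replace the 36-month sentence with wording such as: *Event-free participants are censored at the earlier of 36 months of age and their last completed record check. At interims, those past 36 months whose records have not yet been reviewed to that age are imputed from the last check up to 36 months.* Adjust both predictive steps to match, so that being past 36 months does not by itself make a child complete. State also that the final analysis follows a record review covering each child to 36 months of age; at that point the two rules coincide for children not lost to follow-up.

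The cost is a few sentences in the SAP, a small change to the interim code and, if no such check is already planned, the timing of one retrospective record review. No extra visit is needed. The downside is slightly less person-time at interims.
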